### Assessment

Patients will be assessed after being informed of the objectives of the study and giving their informed consent to participate. Data will be collected following an assessment that will be implemented at baseline and post-treatment (Fig. 1).

**Fig. 1 Fig1:**
[figure not shown]
Study procedure

Patients are diagnosed according to the revised fourth edition of the Diagnostic and Statistical Manual of Mental Disorders (DSM-IV-TR) criteria using the Structured Clinical Interview for DSM-IV-TR, Axis I Disorders [39]. These interviews are carried out independently by two experienced clinicians.

Patients are also assessed with the Mood Disorder Questionnaire [40, 41]. This instrument is a self-report screening test for mood disorders derived from the DSM-IV-TR criteria designed to assess symptoms of bipolar spectrum disorder.

All patients are to be assessed at baseline and post-treatment, in terms of depressive, manic and anxiety symptomatology, psychosocial functioning and lifestyle habits: diet, physical activity and sleep.

Depressive symptoms are measured with the Beck Depression Inventory (BDI-II) [39, 40] and the Beck Hopelessness Scale (BHS) [42, 43]. The BDI-II is a 21-question multiple-choice self-report inventory, one of the most widely used psychometric tests for measuring the severity of depression [39, 40].

The BHS is a 20-item self-report inventory designed to measure three major aspects of hopelessness: feelings about the future, loss of motivation, and expectation [44, 45]. Manic symptoms are assessed with the YMRS [37, 38], an 11-item scale used to assess the severity of this type of symptoms.

Anxiety symptoms are measured with the State-Trait Anxiety Inventory (STAI) [46]. The STAI is composed of 40 items with two subscales: the State Anxiety Scale (S-Anxiety) evaluates the current state of anxiety and the Trait Anxiety Scale (T-Anxiety) evaluates relatively stable aspects of “anxiety proneness”.

The functioning of patients is measured using the Functioning Assessment Short Test [47]. This is a brief instrument designed to assess functional impairment in severe mental disorders. The 24 items of the scale cover 6 specific areas of functioning: autonomy, occupational functioning, cognitive functioning, financial issues, interpersonal relationships, and leisure time.

In addition, all patients are monitored daily by collecting data on the following variables: mind state, number of hours slept, presence of stressful events, adherence and side effects and alcohol and drug use.

### Intervention program

The intervention program consists of nine sessions of online psychoeducation (once a week) focused on patient empowerment by providing specific telecare capabilities and multi-channel communication to enable interaction between the patients and the healthcare professionals (psychiatrists, psychologists and psychiatric nurses).

The psychoeducation comprises learning sessions (with associated assessment questionnaires) and related psychotherapy exercises using their preferred interface (i.e., PC, tablet, or smartphone).

The participants will be able to see the learning status of each assigned learning session and access the related multimedia content. It will be possible to download the associated PDF documents, if participants want, but the video content will only be available online. They will be able to annotate material for the learning sessions and store these notes for future consultation. Once participants have worked through the material for a given learning session, they will have to complete and submit, online, a specific questionnaire to assess their level of understanding.

If the submission process fails, the system should provide appropriate feedback (process failure - subsequent delivery attempt) to the user. If the process succeeds, the system will evaluate the results of the assessment questionnaire, store them along with the usage parameters, provide feedback to the user on the success of the submission process and on the results of the questionnaire, and update the learning status of the learning session (depending on whether they answered the questions correctly). The data collected will be stored in the BPTM environment.

The psychotherapy exercises are ongoing activities that require previous knowledge from the related learning sessions. There are a range of types of exercises on topics such as symptom detection and relapse prevention. Once the related learning session has been successfully completed, the patients will be able to access the related psychotherapy exercises and update them. As it is an ongoing process, the patients will be able to access the psychotherapy exercises over time. The new updates will be sent and stored and the user will get feedback on the status of the data submission process (successful or not). Like for the learning sessions, the data collected will be stored in the BPTM environment.

If clarification is required in relation to learning sessions or psychotherapy exercises, the participants will be able to interact with the psychiatric personnel through asynchronous messages. The user will get feedback on the status of the submission process (successful or not) and the messages will be stored in the BPTM environment.

The system will also be able to, automatically, identify potential alerts. Some examples of alert triggers are: a patient not having started the psychoeducation process after a certain period of time, and a patient “failing” the assessment questionnaire more than once. Patients should receive notifications based on their preferences (e.g., call center call, SMS, instant messaging, or email – to be decided). Alerts handled by the call center will be managed through the OSAREAN platform.

The content of the nine online psychoeducation sessions is as follows:Session 1. *What is bipolar disorder*?Information is provided to the patient about the nature of bipolar disorder (a description of the symptoms that characterize the disorder and biological mechanisms involved).Session 2. *Symptoms of the disorder*
The patient is taught to identify the characteristic symptoms of each phase of bipolar disorder.Session 3. *Course and prognosis of the disorder*
Risk factors that may contribute to worsening the course of the disorder are explained, as are factors related to a good prognosis.Session 4. *Pharmacological treatment for the disorder*
The mechanisms of action of medications are explained, as are potential side effects of the medication, in order to improve adherence and prevent the patient stopping the medication.Session 5. *Relapse prevention*: *risk and protective factors*
The patient is taught to recognize the symptoms that precede a relapse and risk factors that increase the likelihood of relapse, in order to improve the course of their illness.Session 6. *What can be done about a relapse*?It is explained to the patient that rapid identification of the prodromal symptoms and timely intervention can help to prevent relapse and bring him/her back to normal.Session 7. *Healthy lifestyle*
Tips to maintain a healthy lifestyle are provided, seeking to improve the health, quality of life, satisfaction and happiness of the patient.Session 8. *Toxic habits*
The effect of toxic substances on the illness is explained, to motivate the patient to avoid their use, and thereby improve the prognosis of the illness.Session 9. *What can I do to improve my condition*?The patient is taught how to take an active role in their illness to improve their health and quality of life.

### Statistical analysis

Outcomes in each of the groups of patients will be analyzed, to assess whether there has been clinical and/or functional improvement, comparing between baseline and post-treatment by T Student-test for differences in the means of related samples.

The influence of the treatment will be analyzed comparing the clinical and functional improvement in each group through an analysis of covariance (ANCOVA) using the baseline and post-treatment scores.

Finally, logistic regression models will be built to analyze variables potentially associated with relapses and hospitalizations such as sleep, lifestyle, medication adherence, side effects and adverse events.

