#### Specific objective

To assess the effectiveness of a psychoeducation treatment based on telemedicine versus usual treatment in relation to outcomes in bipolar disorder (patients’ illness awareness, symptoms, functionality, relapses and rehospitalizations)To assess satisfaction with the treatment received and the contact with the health service

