### Hypothesis

The online treatment of bipolar disorder will be effective for increasing awareness of the illness, improving depressive and manic symptoms and functionality of patients, and reducing relapses and hospitalizations.Patients receiving online treatment will be more satisfied with the treatment received and their contact with the health service than patients receiving the standard treatment.

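### Relapse and hospitalisation are hypothesised to fall with online treatment, but the stated analysis contains no comparison of these events between the randomised arms

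*Protocol article*

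**What the plan says.** The protocol article's Specific objective is "To assess the effectiveness of a psychoeducation treatment based on telemedicine versus usual treatment in relation to outcomes in bipolar disorder", and the outcomes it lists are "patients’ illness awareness, symptoms, functionality, relapses and rehospitalizations". The Hypothesis section expects the online treatment to be effective for illness awareness, and for "improving depressive and manic symptoms and functionality of patients, and reducing relapses and hospitalizations". Relapse and hospitalisation are therefore outcomes on which the two arms are meant to differ.

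The Statistical analysis section gives three analyses:

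1. Within each group, "comparing between baseline and post-treatment by T Student-test for differences in the means of related samples".
2. For the influence of the treatment, "comparing the clinical and functional improvement in each group through an analysis of covariance (ANCOVA) using the baseline and post-treatment scores".
3. Last, logistic models of "variables potentially associated with relapses and hospitalizations such as sleep, lifestyle, medication adherence, side effects and adverse events".

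Only the third mentions relapse or hospitalisation.

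**The concern.** The objective and hypothesis ask whether assignment to online treatment lowers the risk of relapse and admission. The logistic models ask which patient characteristics go with relapse and admission. Answering the second question does not answer the first.

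At stake is how two named outcomes would be reported. Randomisation protects a comparison of arms. It does not protect an association between, say, adherence and relapse. That association can run either way, since an approaching episode may itself disturb adherence. A reader given only the predictor models could take them as evidence on effectiveness, which they are not.

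**Working it through.** **1. Matching hypothesis to analysis.** The paired t-tests compare means within a group, so they do not compare arms. The ANCOVA does compare arms, but on scores measured at baseline and post-treatment; a relapse or admission during the trial has no such pair of scores. The logistic models concern the events, but their stated purpose is to look for associated variables, and arm is not among the examples. No other section of the article compares these events between arms.

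**2. Would adding arm to the logistic model be enough?** Under Assessment, adherence and side effects are monitored daily; adverse events arise during the trial. Under Intervention program, session 4 aims at adherence and session 7 at lifestyle. Conditioning on post-randomisation values of variables that the intervention is meant to change can remove the part of its effect that acts through them. Sleep and lifestyle are also measured at baseline, and baseline values would not raise this problem. The article does not say which values enter.

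**3. The plan's own sample size.** The Participants section gives 25 per arm for 80% power in a two-sided 5% two-sample t-test. The article gives no effect size, so the figure can only be solved backwards: d = (1.96 + 0.84) × √(2/25) = 0.79, or 0.81 with the exact t distribution. It is a calculation for a difference in means, not for events.

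**4. Events per variable, if all five named variables entered one model.** Assumptions not in the article: annual relapse risk of 30-50%, constant over time, and the counting window.

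Risk over w weeks = 1 − (1 − annual risk)^(w/52); events = 50 × risk; events per variable = events / 5.

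| Window | Annual risk 30% | Annual risk 50% |
|---|---|---|
| 9 weeks | 6.0%: 3.0 events, 0.6 per variable | 11.3%: 5.7 events, 1.1 per variable |
| 26 weeks | 16.3%: 8.2 events, 1.6 per variable | 29.3%: 14.6 events, 2.9 per variable |
| 52 weeks | 30%: 15 events, 3 per variable | 50%: 25 events, 5 per variable |

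Nine weeks is the length of nine weekly sessions.

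**5. What such a model would do.** Simulations used 50 patients and five predictors unrelated to the outcome. The median largest odds ratio per SD was 3.6 to 3.8 with 3 events and 2.6 with 5 events, although every true odds ratio was 1. Separation, where no finite maximum-likelihood estimate exists, occurred in 73-74% of runs with 1 event, 25-29% with 2, 5% with 3, 1% with 4 and under 1% with 5. With a single predictor it was 3% at 1 event and 0% from 3 events up.

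**6. Precision of the missing comparison.** Assumption: treatment halves the control risk. With n = 25 per arm and p̄ the mean of the two risks,

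power = Φ{ [ |p1 − p2|√n − 1.96√(2p̄(1 − p̄)) ] / √( p1(1 − p1) + p2(1 − p2) ) }.

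For 20% v 10%: (0.10 × 5 − 1.96 × 0.505) / 0.5 = −0.98, so power is 16%.

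| Control v online | Expected events, both arms | Power | Power, Fisher | Per arm for 80% |
|---|---|---|---|---|
| 20% v 10% | 7.5 | 16% | 9% | 199 |
| 30% v 15% | 11.25 | 24% | 15% | 121 |
| 40% v 20% | 15 | 34% | 23% | 82 |
| 50% v 25% | 18.75 | 45% | 36% | 58 |

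At 10% v 5%, nearer the 9-week risks in step 4, power is 10% (Fisher 1%).

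**The case against.** The strongest reply is that this is a condensed article and the list of variables is introduced as examples. Arm is unnamed, not excluded, and a fuller document could include it. That stands against a stronger reading that a reader might infer, namely that the plan rules out an arm term and guarantees the hypothesis will never be tested. The text does not support that. It does not remove the point: the article states a kind of analysis for these events, and that analysis addresses a different question from its hypothesis. This is more than an omitted detail.

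Two further strong readings also fail. One is that every listed variable is post-randomisation; sleep and lifestyle are also assessed at baseline. The other is that the logistic model cannot be fitted. The article speaks of models in the plural and does not say that all five variables enter together. Even in a five-variable model, separation is uncommon from 3 events up. The fit would be unstable, not impossible.

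The event counts depend on an assumed risk and window. The article's silence on the window may simply reflect condensation and is not held against it.

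Finally, the missing comparison would have low power. This is true. It lowers the severity and shapes how the result should be reported, but it does not make predictor models a substitute.

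**Conclusion.** The mismatch holds. The article hypothesises a treatment effect on relapse and hospitalisation and states no comparison of either by randomised arm. This rests on the text alone and on no assumed figure. The logistic models cannot stand in for the randomised effect, and adding arm to them with post-randomisation covariates could understate it.

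The sizes are conditional. Events per variable of 0.6-1.1 (9 weeks) or 1.6-5 (26-52 weeks) apply only if all five variables share one model, at the assumed annual risks. Power of 16-45% (Fisher 9-36%) assumes control risks of 20-50% halved by treatment. The point should be fixed. It is not a reason to reject the design, because the stated sample size concerns means and the event outcomes would be imprecise under any analysis.

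**What to change.** In the Statistical analysis section, state that relapse and hospitalisation are each compared by randomised arm, with all randomised patients in their assigned arm. Use a risk difference with an exact confidence interval, or Firth or exact logistic regression with arm as the exposure. Do not adjust for post-randomisation sleep, lifestyle, adherence, side effects or adverse events. Report the result as an estimate with its interval, and say that the trial was not sized for it.

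Label the predictor models exploratory, preferably with baseline values, few predictors and penalised estimation, and draw no conclusion about effectiveness from them.

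If the event comparison is not wanted, narrow the objective and hypothesis so that they no longer claim an effect on relapse and hospitalisation.

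The cost is a change of wording and no new data. The downside is that the event comparison will be imprecise and the predictor models can carry no confirmatory weight.

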## Discussion

Telemedicine is potentially useful to complement usual treatment, helping patients to manage their illnesses, and helping health providers improve the care delivered, especially by giving clinicians feedback. Nevertheless, few randomized clinical trials have shown the effectiveness of this approach in bipolar disorder. The randomized clinical trial described in this paper concerns an internet-based psychoeducation program for bipolar disorder that could have a significant impact on both prognosis and treatment, and may be useful for identifying patients who need earlier and/or continuous therapeutic interventions.

The results of our study may have a significant impact on prognosis of bipolar disorder patients. Below, we set out what our study seeks to accomplish and how:To help healthcare professionals care for as many patients as possible and save time (for both professionals and patients) as well as to collect data for research, the BPTM platform will increase the availability of psychological treatment by providing tele-services (cheaply and with easy access), increase the therapist’s efficiency, reduce the need for face-to-face consultations, allow the involvement of the call center nurses to response promptly to alerts (e.g., by calling patients and/or caregivers) and facilitate patient handover between doctors.To enhance the quality of care, improve the course of the illness, and reduce costs to the healthcare system, the BPTM platform will help clinicians to improve patient follow-up (i.e., achieve closer monitoring of symptoms, and more frequent contact with patients including online consultations), support early identification of risk factors to respond better to patient needs (thereby, reducing relapses, hospitalizations and hospital bed days, and related costs) and provide an additional way to interact with both patients and caregivers (namely, through secure asynchronous messaging).To supply online treatment suited to each patient’s needs, the BPTM platform will allow psychiatric personnel to tailor patient’s treatment (e.g., assignation of learning sessions and questionnaires to be completed by given users, and defining individual patient’s baseline parameters to tune the rules to generate alerts).To provide patients with a way to enhance their knowledge about the management of their own illness and strategies to minimize its consequences (in particular, to reduce psychotic, anxious, manic and depressive symptoms) and to increase their treatment adherence, the BPTM platform will provide access to psychoeducation and psychotherapy in the form of learning sessions (including multimedia content such as video tutorials, presentations, PDF documents and optionally audio) and specific psychotherapy exercises which can be performed wherever and whenever the patient chooses (i.e., ensuring the availability of care for busy patients).To enable patients to be actively involved in their treatment process, the BPTM platform will provide a way to monitor their status remotely by enabling the collection of data on physiological/biometric parameters (either manually or automatically using sensors) and psychological parameters and images (e.g., photographs to identify skin problems), medication intake, and potential medication side effects as well as the course of the illness, by interacting with the system through their preferred available interface (PC, tablet or smartphone, users being asked to utilize devices they already have available, thereby reducing costs and promoting the sustainability of the service). Optionally biometric data could be gathered automatically through mobile devices by connecting to specific biometric sensors (e.g., activity monitors, pulse oximeters, body composition monitors).To allow caregivers to become more involved, increase their knowledge about bipolar disorder and interact with clinicians to be able to better support the care recipients, the BPTM platform will enable their access to specific psychoeducation-related materials and will provide a channel of communication to interact with the psychiatric personnel. It is envisaged that the involvement of caregivers and/or relatives in the treatment will reduce the patient’s acute symptoms by stopping them developing and providing support for early detection. Patient adherence to treatment may also be improved by providing a better family environment and reducing patient anxiety caused by family disputes.To ensure safety, confidentially and privacy, the BPTM platform will comply with all local regulations and implement protocols to safeguard the confidentiality of medical data exchanged.To supply user-friendly interfaces and facilitate personalized interaction, the BPTM platform will allow participants (i.e. patients and caregivers) to use their preferred interface (i.e. PC, tablet or smartphone, as available) and have a common user experience regardless of the choice of device, and allow them to select their preferred channels of communication for notifications. The platform will also support well-known interaction metaphors and usability criteria.

The limitations of this study include difficulties in the management of the new technologies by patients, especially the older ones or those with more cognitive impairment. Likewise, the absence of face-to-face modality in these types of interventions may decrease adherence to the treatment due to a potential weakening of the therapeutic relationship with the therapist and loss of associated benefits. Nevertheless, combined approaches can be implemented, such as using the internet-based platform with additional support from the therapist for some patients.

In conclusion, the platform we propose may help to improve functionality and quality of life in bipolar disorder, and what is most important, the act of bringing different services together (service aggregation) might significantly increase the impact of information and communication technologies on access and adherence to treatment, the quality of the service, patient safety, patient and professional satisfaction, and quality of life of the patients.

## Abbreviations

BDI-II: Beck depression inventory
BHS: Beck hopelessness scale
BPTM: Bipolar patient treatment management
DSM-IV-TR: Diagnostic and statistical manual of mental disorders
FI-STAR: The future internet social and technological alignment research
STAI: State-trait anxiety inventory
